Clinical experience with LIS1 glyco-humanized swine IgG administration. LIS1 is an experimental lymphodepleting polyclonal swine antibody produced by the glyco-humanized GH-pAb platform of Xenothera Laboratory. It is currently in clinical development in kidney transplant patients in EU (EUDRACT 2019-000917-35). So far, the maximal dose that has been reached in the escalating dose arm and found acceptable by the DSMC (which recommended pursuing the trial at this dose) is five daily administrations of 8 mg/kg, i.e., a cumulated dose of 40 mg/kg. Therefore, in this first-in-human trial with XAV-19, we have proposed that the cumulative dose stays inferior to the maximal LIS1 dose administered.Published clinical experience gained with use of convalescent plasma (CP) containing anti-COVID-19 neutralizing antibodies, having evidenced improvement of clinical symptoms. First, critically ill patients with COVID-19 received two consecutive transfusions with 200 mL CP. CP had a SARS-CoV-2-specific antibody (IgG) binding titer greater than 1:1000 and a neutralization titer greater than 40 (end point dilution titers) [9]. In this experience, the ratio between binding and neutralization titers is therefore of 25-fold on the average. Second, Duan et al. treated 10 COVID-19 patients with one dose of 200 mL CP [21]. In this report, the average neutralizing titer calculated on 40 CP was > 1/160. Third, in a former clinical experience with 80 CP transfusions from SARS-convalescent patients in 2003, the average CP volume was 279 mL and the neutralizing titer was > 1/160 [22]. Thus, all together, estimating that transfusion of 200 mL CP corresponds to 25 mg/kg IgG (considering that plasma contains 10 mg/mL IgG and considering 80-kg patients), we can postulate that 25 mg/kg of an IgG preparation presenting a neutralizing titer of at least 1/40 presents a clinical interest. Binding and neutralization titers of glyco-humanized serum from which XAV-19 has been obtained were of approximately 1/100,000 and 1/4000 (in the ELISA neutralization assay). The neutralization titer in a cytopathogenic effect assay was of 1:1600. This neutralizing titer of XAV-19 is thus 40- to 100-fold higher (depending on the assay) as compared with COVID-19 CP presenting a clinical interest according to the literature, and 12.5-fold higher than recommended by the European Commission. It has been considered that the ratio of the neutralization titer in XAV-19 vs CP should be used in the dose selection. According to available data, a batch exhibiting a 40-fold ratio to CP might thus be used at a 40-fold inferior dose, which means that infusions of 0.6 mg/kg XAV-19 should result in similar effects in vivo as compared with 25 mg/kg CP. Recent guidance from the European Commission on use of CP revised desired neutralizing titers of CP and suggested that “neutralizing antibody titers should optimally be greater than 1:320, but lower thresholds might also be effective” (https://www.phc.org.ua/sites/default/files/users/user90/Guidance_plasma_covid19_en.pdf). Therefore, another, higher dose than 0.6 mg/kg XAV-19 might also be tested.PK/PD information obtained from ex vivo assessment of XAV-19. XAV-19 has been assessed in competition ELISA (inhibition of the COVID-19 spike protein binding to ACE-2 receptor) and tested in neutralizing activity assay against SARS-CoV-2 using classical plaque reduction test using Vero cells. Our data showed an IC_50_ (concentration for reaching 50% of maximal signal in the test) of approx. 2.5 μg/mL of the first batch of XAV-19 in these ELISA and neutralization assays [14]. Data from the cytopathogenic effect assay showed a complete inhibition of SARS-CoV-2 infectivity was reached around 15–25 μg/mL in the assay. Considering an average plasma volume of 38.5 mL/kg, infusions of 0.96 mg/kg of this batch of XAV-19 would be required to reach (at Cmax) 25 μg/mL plasma concentration (at Cmax). The volume of distribution of swine glyco-humanized IgG measured in primates (53 mL/kg) has a value close to that of the plasma suggesting that the XAV-19 IgGs will essentially circulate in the plasma. Considering also distribution and elimination half-life, estimated at 172 h in primates, we can select an initial dose 2-fold higher than this target, given on day 1 and day 5, so as to stay above a through level of 25 μg/mL over more than a week, a duration deemed appropriate to obtain a clinical response. The estimated dose to reach this target is 2 mg/Kg.

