#### Interventions description {11a}

Phase 2a will enroll 16 subjects in one of the two dose-level groups: group 1 with dose level defined according to the neutralization titer of the XAV-19 batch (first estimation being 0.5 mg/kg) and group 2 as 4 times higher than group 1 (estimated 2.0 mg/kg). If a patient does not receive the full treatment or has not been followed for 8 days, then he/she will be replaced within the limit of 20 patients in total. Each subject will receive two infusions of XAV-19 or placebo separated by an interval of 4 days (administrations on day 1 and day 5).

More precisely, after enrollment of the first two patients in the low dose group (one patient treated and one patient placebo), data will be obtained after first (day 1) and second (day 5) infusions to collect any severe adverse events that might have occurred, especially in the first 48 h following each infusion.

DSMC will have to review immediately safety data of the first 2 patients (based on day 8 information) and provide advice on continuing enrolment of the 6 last patients of group 1 (low dose). DSMC statement, and sponsor decision with regard to study continuation will be immediately communicated to ANSM.

If there is no signal of severe intolerance by day 8 of enrollment of the first two patients, the rest of the group will be enrolled with the same process of review of tolerance.

When the final patient of group 1 has been enrolled, day 8 safety data of all 8 patients from this low-dose cohort will have to be reviewed by the DSMC to advise of starting high-dose group (group 2). DSMC statement and sponsor decision with regard to study continuation will be immediately communicated to ANSM.

At any time during the phase 2a study, if a serious adverse event occurs, this will be communicated to the DSMC and the sponsor and coordinating investigator will have the responsibility to decide whether DSMC must meet to advise on study conduct.

The same sequential XAV-19 administrations will apply for the second group dosed at 2 mg/kg, with safety steps and DSMC data review.

At the end of phase 2a and as requested by the French regulatory authorities (ANSM), an amendment will be made to the protocol to continue the study in phase 2b.

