The phase 2b (DFD) will be a double-blinded, placebo-controlled randomized study to assess clinical benefit and safety of the phase 2a selected dose of XAV-19 in 352 hospitalized adults with COVID-19-associated moderate pneumonia. Patients will be randomized to either XAV-19 or placebo in a 1:1 ratio and will receive 2 consecutive doses 4 days apart (day 1 and day 5). Obviously, during this 2b study, the DSMC will regularly meet as defined in the DSMC charter.

During the phase 2b study, if the proportion of patients requiring invasive mechanical ventilation after inclusion increases to 30~50% (analyzed by incremental groups of 50 patients), the DSMC will be requested to review data without discontinuation of the study. If the proportion of patients requiring invasive mechanical ventilation after inclusion is greater than 50% of the patients included in the study (analyzed by incremental groups of 50 patients), inclusions will be temporarily stopped and DSMC will be requested to review data and decide on an early definitive discontinuation of the study.

The study diagram of these 2 studies are showed in Figs. 1 and 2.

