### Outcomes {12}

The primary endpoints of the phase 2a study are the (a) pharmacokinetic measurement of the antibody titer of XAV-19 measurements of all treated patients and of all patients in the placebo group at day 8 (3 days after the last administration) and (b) tolerability and adverse events of XAV-19 between the two groups of treated patients and vs. placebo over 29 days, evaluated as:
Occurrence of all suspected XAV-19-related adverse effects and incidence of serious adverse eventsProportion of participants with treatment emergent adverse events leading to study drug discontinuationIncidence of major or bacterial or fungal infections during the hospital stayIncidence of hypersensitivity reactions and infusion reactions. To note AEs are registered up to day 60 and for infusion-related AEs, 48 h after.White cell count, hemoglobin, platelets, creatinine, ALT, AST, on day 1, day 3, day 5, day 8, day 15, and day 29SARS-CoV-2 viral load over time (day 1–day 29), as collected by nasopharyngeal swab samplesTime to RT-PCR virus negativity in nasopharyngeal swab samples

The secondary endpoints of the phase 2a are the:
Pharmacokinetic analysis: Antibody titer measurements at day 1 (pre-dose, post-dose), at day 3, day 5 (pre-dose, post-dose), day 8, day 15, and day 29.The antibody titer of XAV-19 measurements in group 1 treated patients and group 2 treated patients at day 15.Clinical aspects:Duration of supplemental oxygenTransfer to intensive care unit with need for invasive mechanical ventilation or high flow oxygenNormalization of fever ≥24 h: clinical assessment every day from day 1 to day 14. Evaluation to be performed between 8 and 12 am, day X evaluation will consider the higher value during day X-1 (8 am to 8 am)- Normal fever (≤ 37.8 °C tympanic or ≤ 36.6 °C axillary or ≤ 37.2 °C oral taken 4 h apart from antipyretic administration) each day and time to resolution of fever for at least 48 hBiomarkers: CRP, Ferritin (at days 1, 3, 5, 8, 15, and 29)Ordinal scale assessed at Day 15. The 7-point ordinal scale is an assessment of the clinical status at the first assessment on day 15. The scale is as follows:Not hospitalized, no limitations on activitiesNot hospitalized, limitations on activitiesHospitalized, not requiring supplemental oxygenHospitalized, requiring supplemental oxygenHospitalized, on non-invasive ventilation or high flow O_2_ devicesHospitalized, on invasive mechanical ventilation or ECMODeathHospital length of stay

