### Methods for additional analyses (e.g., subgroup analyses) {20b}

The PK Concentration Population included all subjects who received XAV-19 at least once during the study. The PK Summary Population included subjects with an evaluable pharmacokinetic profile of XAV-19 on day 8. The PK/PD Summary Population included subjects who met the criteria for both PP Population and PK Summary Population.

The pharmacokinetic analysis will be evaluated by the study of the accumulation, time-invariance, achievement of steady state, and dose-proportionality by ANOVA models with terms for subjects as a random effect and day as fixed effect.

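### Steady state, and time-invariance in its usual sense, cannot be assessed from two infusions 96 h apart with a 172 h half-life; accumulation can, but only from samples matched on time after dose

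*Protocol article*

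**What the plan says.** The section Methods for additional analyses {20b} names four targets and one type of model: "The pharmacokinetic analysis will be evaluated by the study of the accumulation, time-invariance, achievement of steady state, and dose-proportionality by ANOVA models". The model has subject as a random effect and day as a fixed effect.

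The dosing is in Interventions description {11a}: "Each subject will receive two infusions of XAV-19 or placebo separated by an interval of 4 days", on day 1 and day 5. Phase 2b uses the same two days.

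The kinetic assumption is in Explanation for the choice of comparators {6b}: "elimination half-life, estimated at 172 h in primates". That section justifies the two infusions by keeping levels above 25 μg/mL for more than a week. It does not mention steady state as an aim.

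The sampling is in Outcomes {12}: "Antibody titer measurements at day 1 (pre-dose, post-dose), at day 3, day 5 (pre-dose, post-dose), day 8, day 15, and day 29". Objectives {7} gives the same times for the phase 2b PK sub-study and says that its analyses will be identical to those of phase 2a.

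**The concern.** An assessment of steady state needs enough doses to approach it and at least two end-of-interval troughs to compare. This design has two doses, a dosing interval shorter than the half-life, and one such trough.

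Time-invariance is usually judged by comparing total exposure after a single dose with exposure over one dosing interval at steady state. If steady state is not reached, the second quantity does not exist.

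The model raises a further point. The sampling days fall at different times after the two doses. An overall day effect would therefore reflect elimination as well as accumulation.

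At stake is how the PK results are reported and read. Section {6b} says that safety and PK parameters will guide the choice of the phase 2b dose. Trial status says that phase 2a was completed at the end of December 2020. What can still be improved is the reporting of the phase 2a kinetics and the phase 2b sub-study, which inherits the same analysis.

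**Working it through.** **Inputs, all from the protocol article**
- Doses: 2, with interval τ = 4 days = 96 h ({11a}).
- Half-life: 172 h, a primate estimate; no human value is given ({6b}).
- Volume of distribution in primates: 53 mL/kg; plasma volume: 38.5 mL/kg ({6b}).
- Samples: day 1 pre and post, day 3, day 5 pre and post, days 8, 15 and 29 ({12}).

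**The article's own PK figure.** The dose for 25 μg/mL at peak in the plasma volume is 25 × 38.5 = 962.5 μg/kg, or 0.96 mg/kg. This matches the stated value.

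**Fraction of steady state** (linear one-compartment kinetics, each infusion treated as a bolus)
- Fraction remaining after one interval: r = 2^(−96/172) = 0.679.
- After n doses the fraction of steady state is 1 − rⁿ. For n = 2: 1 − 0.679² = 0.539, about 54%.
- Doses needed at this interval: ln(0.10)/ln(0.679) = 5.95, so 6 doses for 90%; ln(0.05)/ln(0.679) = 7.74, so 8 doses for 95%.

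**How far this depends on the primate half-life.** Two doses reach 90% only if r² ≤ 0.10, that is, a half-life of at most 192 × ln 2 / ln 10 = 57.8 h. For 95% the limit is 192 × ln 2 / ln 20 = 44.4 h. For assumed human values:

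| Half-life (h) | Steady state after two doses |
|---|---|
| 96 | 75% |
| 120 | 67% |
| 172 (article) | 54% |
| 240 | 43% |
| 336 | 33% |
| 504 | 23% |

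**Times after dose, from the sampling schedule**

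| After dose 1 | After dose 2 |
|---|---|
| day 1 post: about 0 h | day 5 post: about 0 h |
| day 3: 48 h | day 8: 72 h |
| day 5 pre: 96 h | day 15: 240 h |
| – | day 29: 576 h |

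Only the two immediate post-dose samples match. Day 5 pre-dose is the only 96 h trough, since no day 9 sample is listed.

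**Time-invariance.** The share of the single-dose AUC to infinity that lies beyond 96 h is r = 68%. The second dose cuts the dose-1 curve off at that point, and no steady-state interval exists for comparison.

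**Accumulation.** The expected ratio of second to first peak is 1 + r = 1.68. The expected ratio of 0–96 h AUC is also 1.68; the dose-2 level at 96 h can be interpolated log-linearly between day 8 (72 h) and day 15 (240 h). The accumulation expected at steady state, 1/(1 − r) = 3.12, could only be projected.

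**The purpose of the schedule is not in question.** At the group 2 estimate of 2 mg/kg and 53 mL/kg, predicted levels are 37.7 (day 1 post), 25.6 (day 5 pre), 63.4 (day 5 post), 47.4 (day 8), 24.1 (day 15) and 6.2 μg/mL (day 29). They stay above 25 μg/mL for 96 + 172 × log₂(63.4/25) ≈ 327 h, or 13.6 days. This agrees with the stated aim of more than a week.

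**The case against.** **A study of whether steady state is achieved may properly report that it was not.** That is true, so a false positive claim need not follow. But the answer is settled by the design for any half-life above about 58 h, and there is no second trough with which to test it. An objective whose answer the data cannot inform should not be listed.

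**The half-life comes from primates.** This stands as a caveat. A longer human half-life makes the problem worse, and a human value would have to be about a third of 172 h before two doses reached 90%.

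**Accumulation can be estimated.** This stands. A reader might infer that the schedule rules out accumulation as well. It does not: the post-dose samples on day 1 and day 5 form a matched pair, and an interval AUC ratio can be approximated.

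**The article names neither the response variable nor the days to be contrasted.** This also stands, and such detail may sit in the full protocol or analysis plan. A reader might infer a definite bias of about 10%, since the predicted levels give 47.4/25.6 = 1.85 for day 8 over day 5 pre-dose and, with 31.1 μg/mL predicted at day 3, 47.4/31.1 = 1.52 for day 8 over day 3, against 1.68. The article does not say that those contrasts will be made. The same model could compare a PK parameter on the two dosing days, where no mismatch arises. What remains is that an overall day effect across the scheduled times would not isolate accumulation.

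**The consequences are limited.** This stands. The article does not make steady state, accumulation or time-invariance a criterion for dose choice.

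**Conclusion.** The point holds for steady state, and for time-invariance in its single-dose versus steady-state sense. On the article's own half-life and schedule, the last dose reaches about 54% of steady state, washout follows, and one 96 h trough is sampled. This rests on linear one-compartment kinetics and a primate half-life, and survives any half-life above about 58 h.

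For accumulation the point is narrower. A two-dose ratio is obtainable, expected at about 1.68, provided that samples are matched on time after dose. The day-effect model as described does not ensure this.

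The affected analysis is secondary in phase 2a and ancillary in phase 2b. The day 8 titre endpoint, tested by Kruskal-Wallis, and the phase 2b comparison of time to oxygen weaning do not depend on it. A reader might infer that the dosing schedule or the dose choice is undermined; nothing here supports that.

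**What to change.** In Methods for additional analyses {20b}, and so in the phase 2b PK sub-study:

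1. Delete achievement of steady state from the list of targets.
2. Define accumulation as the ratio of the day 5 post-dose to the day 1 post-dose level, with both samples taken at the same delay after infusion. The alternative is the ratio of 0–96 h AUC after dose 2 to that after dose 1, with the dose-2 level at 96 h interpolated between day 8 and day 15.
3. Assess time-invariance by comparing the levels observed after dose 2 with those predicted by superposition from dose 1, in place of a day-effect test. A compartmental model fitted to all samples is one way to do this, but is not required.

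The cost is a little more analysis work and the loss of the steady-state claim. The superposition check will have limited precision: the dose-1 samples cover 96/172 = 0.56 of a half-life, and phase 2a has six treated patients per dose level. Results should be given as estimates with intervals. No new samples, visits or dosing changes are needed.

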### Methods in analysis to handle protocol non-adherence and any statistical methods to handle missing data {20c}

For phase2a study, no imputation will be realized in this study. Patient who did not receive both doses or followed up until D8 will be replaced. For phase 2b, we do not expect missing data for the primary outcome. However, if patient is followed up then data will be censored at last known date. No imputation will be used for secondary efficacy and safety outcomes. No subject replacement is planned.

### Plans to give access to the full protocol, participant-level data, and statistical code {31c}

According to French law, the results of the study will be published on the website of the regulatory authority. Data sharing will be between the investigators only. However, the datasets analyzed during the current study will be available from the corresponding author on reasonable request. Furthermore, the sponsor will enter the study results in the European Union database as soon as the main publication from the research is released, in order to preserve intellectual property.

## Oversight and monitoring

### Composition of the coordinating center and trial steering committee {5d}

It has been possible to carry out the protocol and the trial thanks to a Scientific Committee created and coordinated by Dr. [name]. The Scientific Committee’s missions are:
Approval of DSMC compositionTo ask for information regarding the progress of the research project, any potential issue, and available resultsTo ensure compliance with ethics requirementsTo perform the scientific follow-up of the research: maintain the relevance of the research objectives and the permanent validity of the methods implemented to meet themTo make all important decisions at the demand of the Coordinating Investigator or the DSMC regarding the good conduct of the research in compliance with the protocol, any procedure specific to the research, and Good Clinical PracticesTo decide on all relevant modification of the protocol required to achieve the research project (including recruitment facilitating measures, protocol amendments before regulatory submissions, addition or closure of participating sites)To provide information to all investigators and other participants in the research,To ensure that rules related to data and biological samples access are followed,To ensure that rules related to the communication and publication of research results are fulfilled

Meeting minutes are drafted following each meeting by the Project Leader, together with the president of the Scientific Committee (at least an exhaustive list of the issues discussed and the decisions made as well as the list of the points raised). The minutes are submitted for review and modifications to the members of the Scientific Committee present at the meeting. The minutes are then validated by the president of the Scientific Committee. It is then distributed to the Scientific Committee members and to the persons invited to the meeting, as well as to the Head of the Nantes Hospital clinical research department. The minutes are definitely adopted at the beginning of the following meeting of the Scientific Committee.

### Composition of the data monitoring committee, its role and reporting structure {21a}

The role of the DSMC is to review the progress of the trial and the accumulating data to detect evidence of early safety issues for the enrolled subjects. The DSMC will give recommendation regarding modification to the ongoing conduct of the trial (see Figs. 1 and 2) and give approval for continuing the study to the next step within each group of phase 2a and between the phase 2a and 2b.

The competent members in the field of clinical trials (disease and methodology) are not involved in the study. They are appointed for the period of the study and undertake to participate and to respect the data confidentiality.

The annual safety report is sent to the Data and Safety Monitoring Committee. The committee may be requested for a review by the person in charge of safety pharmacology if a SUSAR or a SAE presents a particular analytical problem or if a doubt in respect benefit/risk arises during the study.

### Adverse event reporting and harms {22}

All patients will be closely monitored during both study phases for overall biological and clinical safety data (e.g., infections or malignancies) and any drugs toxicity.

According to regulation, each AE reported by the patient or identified by the investigator must be collected and reported to sponsor, as soon as he is aware, if it meets to seriousness criteria from inclusion of the subject, to the end of the participation.

As a routine precaution, patients enrolled in this trial must be observed for at least 2 h post infusion of study drugs. Patients will be assessed for signs or symptoms of any infusion reactions (e.g., hypotension, hypoxia, tachycardia, fever, nausea, fatigue, headache, myalgia, and malaise).

